# Cytokine adsorption in patients with acute-on-chronic liver failure (CYTOHEP)—a single center, open-label, three-arm, randomized, controlled intervention trial

**DOI:** 10.1186/s13063-022-06139-6

**Published:** 2022-03-18

**Keywords:** Liver cirrhosis, Acute-on-chronic liver failure, Extracorporeal hemoadsorption, CytoSorb, Randomized controlled trial

## Abstract

**Background:**

Liver cirrhosis is a major healthcare problem and the mortality rate is high. During recent years, systemic inflammation has been recognized as a major driver of hepatic decompensation and progression of liver cirrhosis to acute-on-chronic liver failure (ACLF). The aim of the CYTOHEP study is to assess the impact of extracorporeal hemoadsorption with the CytoSorb adsorber on serum bilirubin concentrations, humoral inflammation parameters, liver function parameters, and patient survival in patients with ACLF and acute kidney injury (AKI).

**Methods:**

The CYTOHEP study is a prospective, single-center, open-label, three-arm, randomized, controlled intervention trial. Patients with ACLF and AKI stage 3 according to Kidney Disease: Improving Global Outcome (KDIGO) criteria will be randomized into three groups to be treated with (1) continuous renal replacement therapy (CRRT) and CytoSorb, (2) CRRT without CytoSorb, and (3) without both, CRRT and CytoSorb. In the hemoadsorption group, CytoSorb will be used for 72 h. The other groups receive standard of care with early or late initiation of CRRT, respectively. Primary endpoint of the study is serum bilirubin concentration after 72 h, important secondary endpoints are 30-day survival and a panel of inflammatory parameters.

**Discussion:**

The CYTOHEP study is designed to evaluate the benefit of extracorporeal hemoadsorption in patients with ACLF. The results of this study will help to better understand the potential role of hemoadsorption for the treatment of ACLF and its impact on bilirubin levels, inflammatory parameters, and survival.

**Trial registration:**

ClinicalTrials.gov NCT05019352. Registered on August 24, 2021. Deutsches Register Klinischer Studien (DRKS) DRKS00026082.

## Clinical Trial Protocol

**Table Taba:** 

1. **Administrative Information**	
1.1. **Title**	
Cytokine adsorption in patients with acute-on-chronic liver failure (CYTOHEP)—a single center, open-label, three-arm, randomized, controlled intervention trial	
1.2. **Trial registration**	
1.2.1. **Trial registry name and trial identifier**	
ClinicalTrials.gov: NCT05019352	
Deutsches Register Klinischer Studien (DRKS): DRKS00026082	
1.2.2. **Synopsis/World Health Organization Trial Registration Data Set**	
**Data category**	**Information**
Primary registry and trial identifying number	ClinicalTrials.gov: NCT05019352
Date of registration in primary registry	August 24, 2021
Secondary identifying numbers	DRKS00026082
Source(s) of monetary of material support	University of Freiburg, Medical Center, Department of Medicine III, Intensive Care Medicine, Faculty of Medicine, University of Freiburg
Primary sponsor	University of Freiburg, Medical Center, Department of Medicine III - Intensive Care Medicine
Secondary sponsor(s)	None
Contact for public queries	University of Freiburg
[name], MPH	Medical Center Department of Medicine III - Intensive Care Medicine [name] Germany [contact] [contact] E-mail: [contact]
Contact for scientific queries [name], MPH	University of Freiburg Medical Center Department of Medicine III - Intensive Care Medicine [name] Germany [contact] [contact] E-mail: [contact]
Public title	Cyctokine adsorption in acute-on-chronic liver failure (CYTOHEP trial)
Scientific title	Cytokine adsorption in patients with acute-on chronic liver failure (CYTOHEP) – a single center, open-label, three-arm, randomized, controlled intervention trial
Countries of recruitment	Germany
Health condition(s) or problem(s) studied	Liver cirrhosis; acute-on-chronic liver failure (ACLF)
Intervention(s)	Active comparator: continuous renal replacement therapy with cytokine adsorption for 72 h control comparator: continuous renal replacement therapy without cytokine adsorption control comparator: no continuous renal replacement therapy and no cytokine adsorption
Key inclusion and exclusion	Inclusion criteria • Adult patients (≥ 18 years) admitted to the University Medical Center Freiburg, Germany • Acute-on-chronic liver failure (ACLF) [1] **WITH** o Acute kidney injury according to Kidney Disease: Improving Global Outcome (KDIGO) criteria stage 3 (≥ 3-fold increase of serum creatine **OR** increase of serum creatine ≥ 4 mg/dl **OR** urine output ≤ 0.3 ml/kg/h for ≥ 24 h **OR** anuria for ≥ 12 h) **AND** o Serum bilirubin ≥ 5 mg/dl Exclusion criteria • Known patient will against participation in the study or against the measures applied in the study • A decision made prior to inclusion to stop further treatment of the patient within the next 24 h • No complete remission of malignancy including hepatocellular carcinoma within the past 12 months • Patients on the waiting list for liver transplant or the potential option for being listed for liver transplant within the next 6 months • Liver cirrhosis in patients after liver transplantation • Ongoing intermittent or continuous renal replacement therapy before study inclusion All patients that fulfill all inclusion criteria and none of the exclusion criteria, will be considered *provisionally eligible*. In a subsequent assessment it will be ascertained whether the most responsible clinician(s) (the attending critical care physician and where relevant, the attending nephrologist) are in a position of clinical equipoise with respect to the two renal-replacement therapy initiation strategies that the provisionally eligible patient would receive if he/she was randomized. This will be performed in practice by ascertaining the presence of the following two exclusion criteria: • Clinician(s) caring for the patient believe that immediate renal-replacement therapy is mandated. After fulfilling the above inclusion/exclusion criteria, the study team has to speak to the ICU and/or nephrology attending physician and ask if he/she agrees with the statement: “Renal-replacement therapy must be initiated immediately for this patient.” If the answer is “Yes”, the patient will be excluded but could be re-screened for eligibility, if applicable. • Clinician(s) caring for the patient believe that deferral of renal-replacement therapy is mandated. After fulfilling the above inclusion/exclusion criteria, the study team has to speak to the ICU and/or nephrology attending physician and ask if he/she agrees with the statement: “Renal-replacement therapy must be deferred for this patient.” If the answer is “Yes”, the patient will be excluded, but could be re-screened for eligibility. When on both questions above it will be replied “No” by all of the relevant clinicians, the respective patient will be considered fully eligible for study participation.
Study type	Interventional Allocation: randomized; Intervention model: parallel assignment; Masking: open-label Primary purpose: treatment of severe acute-on-chronic liver failure Post-approval/pivotal study
Date of first enrollment	December 12, 2021
Target sample size	51
Recruitment status	Recruitment phase
Primary outcome(s)	Serum bilirubin reduction after 72 h
Key secondary outcomes	• Survival time (days) from baseline • Interleukin-6 after 72 h • Liver function parameters (72 h): Quick/INR, AST, ALT, AP, g-GT • Blood lactate (72 h) • Clinical scores: CLIF-SOFA-score, MELD score, SOFA score, SAPS II and FIPS score (72 h) • Ventilator free days (VeFD) in the first 30 days after randomization, where each day on invasive mechanical ventilation (IMV), non-invasive ventilation (NIV), or ECMO is defined as ventilator day. VeFD=0, if the patient dies in the first 30 days after randomization • Vasopressor free days (VaFD) in the first 30 days after randomization, where each day with any dose of epinephrine, norepinephrine, dobutamine, argipressin or terlipressin is defined as vasopressor day. VaFD=0, if the patient dies in the first 30 days after randomization • Dialysis free days (DFD) in the first 30 days after randomization, where each day on renal replacement therapy (RRT) is defined as dialysis day. DFD=0 if the patient dies in the first 30 days after randomization • A biomarker panel of pro- and anti-inflammatory cytokines (blood samples will be frozen and stored for later analyses, panel will be determined at the time of analysis)
1.3. **Protocol version**	
Version 1.3, 27.01.2022 Revision chronology:	
	• Version 1.0; submitted to IRB for approval (02.07.2021); revision requested by IRB (05.08.2021) • Version 1.1; revised version, considering previous request by IRB (09.08.2021); IRB approval (17.08.2021) • Version 1.2.; amendment submitted to IRB (04.10.2021); addition of trial registration information, specification of randomization tool; IRB approval (19.10.2021)

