#### Interventions

##### Description of study plan and interventions

The study is a prospective, randomized, open-label intervention study. Only patients with acute-on-chronic liver failure and AKI KDIGO stage 3 are included. In the CRRT with CytoSorb group, a CytoSorb adsorber is incorporated into the CRRT system for a total of 72 h. The adsorber is usually installed in the system as part of the preparation of the CRRT system before the system is connected to the patient circuit, but at the latest within 4 h after initiation of CRRT. The first adsorber can be left in the system for 12 h (± 6 h) and must then be replaced (*t*_12_). The replacement of the second adsorber will be 24 h after the start of adsorption therapy (*t*_24_). The third adsorber will be replaced at 48 h (*t*_48_) and the fourth adsorber will be removed at 72 h (*t*_72_) after the initial start of adsorption therapy. For the change adsorber 2 and 3 and the removal of adsorber 4 there will be a tolerance interval of ± 2 h for the respective time point (24 h, 48 h, and 72 h, respectively). Adsorber therapy will be applied for a total duration of 72 h using 4 adsorbers. In case of blood clotting in the adsorber and the CRRT circuit or any other reason for loss of function of CRRT with or without cytokine adsorption during the first 72 h, the CRRT system or the adsorber should be replaced as soon as possible. The therapy in the CRRT without the CytoSorb group differs from the intervention group only in that no CytoSorb adsorber is incorporated into the CRRT system. In the third group, patients received neither CRRT nor CytoSorb (Fig. 1).

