Therapy of liver failure and potential concomitant complications of other organs will follow established standards and guidelines. In the CRRT with CytoSorb group, the CytoSorb adsorber will be connected pre-dialysis filter via a closed-loop circuit to the CRRT pump (multiFiltratePro, Fresenius Medical Care, see Fig. 2 for the setup). Recommended flow rates through the adsorber are between 100 ml/min and 700 ml/min. The choice of anticoagulation for the CRRT will be left to the discretion of the nephrologist on call. CRRT will be continued for at least 72 h and can then be stopped or continued by the discretion of the treating nephrologists or intensivists. CRRT dose can be calculated based on the effluent flow rate (= (dialysis flow in ml/hour + ultrafiltration rate in ml/hour)/body weight in kg). The recommended dose according to the KDIGO guideline is 20–25 mL/kg/h [22]. We will be aiming at approximately 25 mL/kg/h in order to achieve (despite interruptions and CRRT downtime, which are inevitable) a minimum effluent rate of 20 mL/kg/h over a 24-h period.

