#### Outcomes

##### Primary endpoint

The primary endpoint is serum bilirubin level after 72 h. The reference time (*t*_0_) is the start of cytokine adsorption in the CRRT with the CytoSorb group and the start of CRRT in the CRRT without the CytoSorb group. In the no CRRT group, the reference time (*t*_0_) will be the time of randomization plus 2 h (since this is the expected average duration between randomization and initiation of CRRT in the CRRT groups).

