#### Sample size

In this study, the randomization to the treatment arms CRRT with CytoSorb, CRRT without CytoSorb, and no CRRT will be done with a 1:1:1 ratio. The group with no CRRT is included merely for exploratory analysis of safety aspects and does not affect the power analysis. The sample size calculation is motivated by data from case reports and retrospective case series, according to which serum bilirubin levels in patients with liver failure could be reduced by 50% by adsorption in the CytoSorb adsorber for 72 h [17–20]. We expect a mean of 10 mg/dl serum bilirubin at baseline, no change in control patients, and a reduction to a mean of 5 mg/dl after 72 h in the cytokine adsorption group. The typical range, 1 to 20 mg/dl, implies an expected standard deviation of about 5 mg/dl. This is a conservative estimate, as the inclusion criterion, bilirubin >5mg/dl, was not considered for the calculation. On the basis of a two-group *t*-test with a two-sided significance level of 5%, a sample size of 17 patients in each group yields a power of 80% to detect a difference if it is assumed that the mean serum bilirubin levels after 72 h differ by 5 mg/dl, given a standard deviation of 5 mg/dl in both groups. This is conservative in that we anticipate a lower standard deviation after 72 h in the intervention group. No missing values up to 72 h are expected. Hence, the numbers of patients to be randomized to the three treatment arms are *n*=17:17:17.

In the unexpected event that patients die within the study before reaching the 72-h end point, we will describe an appropriate expansion of enrolment in an amendment to this study protocol.

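### The exclusion for an already decided stop of treatment looks 24 h ahead, while study treatment and the primary endpoint run to 72 h

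*Protocol article*

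**What the plan says.** The criterion stands in the protocol article under Subject exclusion criteria and, in the same words, in the synopsis table: "A decision made prior to inclusion to stop further treatment of the patient within the next 24 h".

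The other intervals that bear on the primary comparison are longer:

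- Description of study plan and interventions, adsorber arm: "Adsorber therapy will be applied for a total duration of 72 h using 4 adsorbers".
- Same section, CRRT: "CRRT will be continued for at least 72 h".
- Primary endpoint: "The primary endpoint is serum bilirubin level after 72 h". The clock starts at t0, which is the start of adsorption or of CRRT. In the no CRRT arm it is set at 2 h after randomisation, because that is the expected average delay in the CRRT arms.
- Sample size: "No missing values up to 72 h are expected". Death before 72 h is treated as unexpected and would lead to an expansion of enrolment by amendment.
- Definition of analysis population: patients are analysed as randomised even if they discontinue treatment, but deaths within 72 h are left out of the primary analysis. No other kind of missing primary data is expected.

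**The concern.** The entry rule screens for a foreseeable stop of treatment over only the first third of the interval that the endpoint needs (24/72). Suppose the team has decided before inclusion to stop treatment at 36 or 48 h. No listed criterion excludes that patient: the exclusion for known patient will concerns refusal of the study or its measures, and the two equipoise questions concern only whether renal replacement must start at once or must be deferred.

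Three things are at stake.

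- **Primary endpoint.** The patient takes one of 17 places in an arm and may contribute nothing to the primary comparison, in a calculation with no allowance for loss.
- **Survival.** Survival time is named as the most relevant secondary endpoint and is to be used to size the next trial. A death that follows a decision made before randomisation enters those data.
- **Safety review.** Under Early termination of the study, each death is assessed before another patient is included. A death foreseeable at screening adds noise to that review.

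Unlike other early losses, these could be identified before randomisation.

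**Working it through.** **Step 1: compare the windows.**

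| Item | Interval | Counted from |
|---|---|---|
| Exclusion for a decided stop | 24 h | inclusion |
| Adsorber treatment | 72 h | start of adsorption |
| CRRT in the CRRT arms | at least 72 h | start of CRRT |
| Primary endpoint | 72 h | t0, about 2 h after randomisation |
| Period assumed free of missing values | 72 h | as for the endpoint |

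The endpoint falls at about 2 + 72 = 74 h after randomisation. The uncovered part therefore runs from 24 h to roughly 74 h.

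**Step 2: reproduce the plan's power.** The inputs come from Sample size: two-group t-test, two-sided 5%, means that differ by 5 mg/dl ("the mean serum bilirubin levels after 72 h differ by 5 mg/dl"), SD 5 mg/dl in both groups and 17 per arm. The plan states that "a sample size of 17 patients in each group yields a power of 80" per cent.

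The noncentrality parameter is δ = 5 / (5·√(1/n₁ + 1/n₂)), with n₁ + n₂ − 2 degrees of freedom. Power is the probability that a noncentral t variable with this δ exceeds the two-sided 5% critical value in absolute size.

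For 17 vs 17, δ = 1/√(2/17) = 2.916, df = 32 and the critical value is 2.037. Power is 80.7%, so the plan's figure reproduces, given no losses.

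**Step 3: remove patients.**

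| Evaluable | δ | df | Critical value | Power |
|---|---|---|---|---|
| 17 vs 17 | 2.916 | 32 | 2.037 | 80.7% |
| 17 vs 16 | 2.871 | 31 | 2.040 | 79.4% |
| 16 vs 16 | 2.828 | 30 | 2.042 | 78.1% |
| 15 vs 15 | 2.739 | 28 | 2.048 | 75.3% |

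One lost patient is 1/17 = 5.9% of an arm and costs 80.7 − 79.4 = 1.3 percentage points. The figure of 78.1% needs one loss in each powered arm. A loss in the no CRRT arm does not touch the powered comparison.

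The number lost is an assumption: the documents give no rate of stops decided for 24 h to 72 h. The table covers 0 to 2 per powered arm.

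**Step 4: allow for the planned analysis.** The primary model adjusts for baseline bilirubin, which the protocol expects to raise power. The correlation between baseline and 72-h values is not given. If it were 0.3 (an assumption), the residual SD would be 5·√(1 − 0.09) = 4.77, δ at 16 vs 16 would be 2.828/0.954 = 2.965, and power would be about 82%. A modest correlation would thus offset one loss per arm.

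**The case against.** The strongest reply is that nothing here is a contradiction. An exclusion window need not equal the endpoint interval, and the protocol does not say that this criterion is meant to secure complete data at 72 h. The synopsis and the main text agree with each other. Every patient is discussed with the attending physicians before randomisation, and a team with a dated decision to stop treatment that also accepts randomisation to 72 h of CRRT is a hypothetical case. The protocol also foresees expanding enrolment if patients die before 72 h.

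Most of this stands as a limit on size. The equipoise discussion and the patient-will exclusion narrow the gap in practice, but neither closes it. The expansion by amendment is a remedy after the event; it does not stop an avoidable loss from being randomised.

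A reader might infer that such patients are already known not to reach the endpoint. The documents do not support that. Stopping treatment is not death, patients who discontinue stay in the analysis as randomised, and only deaths within 72 h are removed. A patient alive at 72 h can still be measured.

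A reader might also infer bias in survival. Randomisation spreads these patients over the arms in expectation, so the expected effect is noise. Survival is followed to day 90 in any case, so a window ending at 72 h would remove only some such deaths. The case for 72 h rests on the primary endpoint.

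**Conclusion.** The point holds as a mismatch between an eligibility window and the interval that the trial needs. A patient with a stop of treatment already decided for the time between 24 h and the 72-h measurement passes the written criteria. Incomplete study treatment is then expected, and a missing 72-h bilirubin is likely but not certain.

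The effect is small per patient: 1.3 points of power for one loss in one powered arm and 2.6 points (80.7 − 78.1) for one in each. These figures rest on the plan's own difference and SD, on the unadjusted t-test, and on the patient in fact supplying no value. The frequency is unknown and may be near zero, so the documents do not support a claim that the trial is materially underpowered for this reason. The change is worth making because it is cheap and the calculation has almost no margin: the first loss in a powered arm already takes the unadjusted figure below 80%.

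**What to change.** Reconcile the criterion, under Subject exclusion criteria and in the synopsis, with Description of study plan and interventions, Primary endpoint, Sample size and the definition of the analysis population. The exclusion should cover decisions, already made before inclusion, to stop treatment before the 72-h primary endpoint measurement, defined as 72 h after t0. Tying the window to the measurement is more exact than 72 h from inclusion, which would end about 2 h too early.

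The change concerns only who may be randomised. It sets no rule on when treatment should stop and alters no patient's care.

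The cost is a short amendment in two places, with ethics approval. A few patients become ineligible, and some of them might still have supplied a 72-h value.

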
## Introduction

### Background and rationale

#### Systemic inflammation in decompensated liver cirrhosis and acute-on-chronic liver failure (ACLF)

Liver cirrhosis is a major healthcare problem. Among affected patients mortality is high. In Germany, in 2015 more than 13,000 patients died owing to decompensated cirrhosis [2]. The clinical course of cirrhosis can be separated in compensated and decompensated cirrhosis. Patients with compensated cirrhosis are largely asymptomatic and the development of decompensating events is a major hallmark in the course of the disease as median survival decreases from 12 years to less than 2 years [3]**.** The most important decompensating events are the development of variceal bleeding, ascites, hepatic encephalopathy, and bacterial infections [4]. Previously, liver cirrhosis has been described as a systemic disease affecting almost any other organ system [4, 5]. The development of extrahepatic organ complications in decompensated cirrhosis has been identified as a major prognostic milestone and has been described as acute-on-chronic liver failure (ACLF) [6]. ACLF is understood as a dynamic process and may evolve within days leading to multi-organ failure with renal failure being the most common organ involvement (56%), followed by liver and coagulation failure (44% and 28%, respectively) [6, 7]. ACLF is associated with a high 28-day mortality ranging from 22% to 77% in patients with multi-organ failure [6].

During recent years, systemic inflammation has been recognized as a major driver of hepatic decompensation and progression of liver cirrhosis to ACLF. Systemic inflammation steadily increases with the progression of decompensated liver cirrhosis and the development of ACLF [4, 8]. Importantly, systemic inflammation was described as an important trigger for the development of extrahepatic organ failures, such as renal failure, development of hepatopulmonary syndrome, cirrhotic cardiomyopathy, and hepatic encephalopathy [4, 9, 10]. The evolution of systemic inflammation in patients with progressing hepatic decompensation and ACLF is due to an increase in bacterial translocation in the intestine [4, 11]. Bacterial translocation is associated with portal hypertension which is one of the major drivers of decompensation in cirrhotic patients and determines a hallmark in the course of disease [4, 12]. Damage-associated molecular patterns (DAMPs) and pathogen-associated molecular patterns (PAMPs) may serve as a surrogate for bacterial translocation in patients with liver cirrhosis [4]. In summary, systemic inflammation is particularly relevant in the pathogenesis of acute hepatic decompensation and is also associated with reduced survival [13]. Therefore, elimination of PAMPs, DAMPs, and inflammatory cytokines in addition to established therapeutic approaches aiming at a reduction of bacterial translocation and mitigation of portal hypertension may help control excessive inflammatory activity and thus support hepatic recompensation. This may ultimately lead to improved survival.

Previous in-vitro examinations and studies in non-cirrhotic inflammatory disorders have shown that proinflammatory cytokines, DAMPs, and PAMPs can effectively be removed by extracorporeal hemoadsorption in the CytoSorb adsorber [14].

